#### Level of Significance and Power

In the interim analysis (described below), the DSMB will use Pocock stopping boundaries (*P*<.03). Therefore, the 2-sided α value in the final analysis will be *P*=.03. We will use a power of 0.8 (80%).

#### Sample Size

The power calculation, performed using GPower 3.1 (AdvanSci Research Solutions), is based on superiority analysis assumptions for the primary end point (improved oxygenation ratio, defined as the highest PaO_2_/FiO_2_ ratio measured within 72 h after LTx). Based on data from a cohort of patients undergoing LTx from Skåne University Hospital in Lund from 2011 to 2020, we estimate that the mean PaO_2_/FiO_2_ value in the control group will be approximately 300 (SD 100) mm Hg and that values will be normally distributed. We estimate that the average PaO_2_/FiO_2_ value will be 60 (SD 100) mm Hg higher (effect size) in the treatment group compared with the control group.

The sample size was calculated using a 2-tailed *t* test to compare the PaO_2_/FiO_2_ values in the treatment versus control groups. We will require 52 participants in each group to achieve the power and α level detailed above. We will add 10% of the required sample size to account for possible dropouts, withdrawal of consent, or mortality in the first 72 hours. Thus, we aim to recruit 58 patients in each group to a total of 116 participants. With this number of participants, we estimate that all secondary outcome variables will have a power of at least 80% at an α level of .05.

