#### Secondary Performance End Points

The secondary end points are (1) plasma levels of inflammatory markers: interleukin (IL)-10, IL-1β, soluble IL-2 receptor, IL-6, IL-8, and tumor necrosis factor α before and immediately after transplantation and at 6, 12, 24, 48, and 72 hours after transplantation and C-reactive protein and white blood cells before and immediately after transplantation and at day 1, 2, and 3 after transplantation; (2) infiltrates and oedema measured by chest x-ray or CT scan of the thorax at day 1, 2, and 3 after transplantation; (3) highest daily arterial blood gas measurements recorded on day 1, 2, and 3 after transplantation, as a measure of lung function; (4) PGD severity as evaluated per standard clinical procedures using a rating scale from 0 to 3 on day 1, 2, and 3 after transplantation, as a measure of lung function; (5) presence of any grade of PGD on day 1, 2, and 3 after transplantation, as a measure of lung function; (6) total dose of norepinephrine administered in the first 72 hours; (7) mortality up to 48 months after transplantation; (8) lung diffusion capacity, measured by carbon monoxide diffusion, at 6, 12, 24, and 48 months after transplantation, as a measure of lung function; (9) forced expiratory volume, forced vital capacity, and total lung capacity measured by spirometry at 1, 3, 6, 12, 24, and 48 months after transplantation, as a measure of lung function; (10) occurrence of any acute rejection episodes (clinically treated and/or biopsy verified) up to 48 months after transplantation, as a measure of lung function; (11) chest CT findings at 1, 3, 6, 12, 24, 36, and 48 months after transplantation; (12) the presence of any CLAD and CLAD subtypes up to 48 months after transplantation, as a measure of lung function; (13) kidney function evaluated by measurement of serum creatinine levels; calculated glomerular filtration rate and need for renal replacement therapy on day 1, 2, and 3 and at 1, 3, 6, 9, 12, 24, and 48 months after transplantation; urea levels on day 1, 2, and 3 after transplantation; and iohexol-clearance at 3, 6, 9, 12, 24, 36, and 48 months after transplantation; and (14) QOL evaluated by the 36-Item Short Form Health Survey at 24 and 48 months after transplantation.

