#### Interim Analysis

The DSMB will perform an interim analysis of the primary outcome after at least 30 participants for each group have undergone LTx and reached the intervention period and the 72-hour time point has been passed for the 30th participant in each group. The DSMB will use Pocock stopping boundaries (*P*<.03) as the statistical limit to guide its recommendations regarding early termination of the trial on the basis of rejecting the null hypothesis. If the *P* value for the primary outcome is below .03 at the interim analysis, then a decision will be taken by the trial management team to either stop the trial early or to continue recruitment. This has been accounted for in the sample size calculation above, and no additional adjustments for multiple testing are necessary.

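### The claim of at least 80% power for all secondary outcomes has no stated basis, and for mortality it is untenable unless the hazard is more than halved

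*Protocol article*

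**What the plan says.** The Sample Size section of the protocol article takes a control mean of 300 mm Hg, a difference of 60 and an SD of 100 in both arms, compared by a two-tailed t test. The significance level comes from Level of Significance and Power: "Therefore, the 2-sided α value in the final analysis will be" .03, with 80% power. The result is "We will require 52 participants in each group to achieve the power and α level detailed above". After a 10% allowance, "we aim to recruit 58 patients in each group to a total of 116 participants".

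The same paragraph ends by extending the power statement to every secondary endpoint at that sample size: "we estimate that all secondary outcome variables will have a power of at least 80% at an α level of .05".

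Secondary Performance End Points lists 14 groups of outcomes. Some are continuous (inflammatory markers, spirometry, diffusion capacity, creatinine). Others are binary or time-to-event: any PGD on days 1 to 3, acute rejection, CLAD, need for renal replacement, and "mortality up to 48 months after transplantation". The article gives no treatment effect for any of them. Its only incidence figure is in the Introduction, which puts PGD and CLAD at 40% to 80%.

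**The concern.** Power has a value only for a stated effect and, for event outcomes, a stated rate. The one calculation shown concerns a continuous outcome with a standardised difference of 0.6. That says nothing about a binary or survival outcome, and it covers another continuous outcome only if its effect is nearly as large.

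What is at stake is interpretation. The stated purpose is superiority across PGD, lung and kidney function, survival and quality of life, and the Conclusions hypothesise better overall survival. A reader told that every secondary outcome has 80% power could take a non-significant mortality, CLAD, rejection or PGD result as evidence of no benefit. For plausible effects the trial may have had little chance of detecting one.

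**Working it through.** **1. The plan's own figure.** Inputs from Sample Size and Level of Significance and Power: d = 60/100 = 0.6, two-sided alpha .03, power 80%, 1:1 allocation. The noncentral t distribution gives 52 per arm (power 80.3%). The 10% allowance gives 52 × 1.1 = 57.2 or 52/0.9 = 57.8, both rounding up to 58. The primary sample size reproduces.

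The secondary power figure cannot be reproduced, because the article supplies no inputs for it. The steps below ask instead what effect it would require, at two-sided .05 and 58 per arm.

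**2. Continuous outcomes.** Approximately, d = (1.96 + 0.8416) × √(2/n). For n = 58 this is 2.8016 × √(2/58) = 0.520. The noncentral t gives 0.525, and 0.555 at 52 evaluable per arm. The claim therefore needs effects almost as large as the primary one.

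**3. Binary outcomes at one time point.** Normal approximation with pooled null variance, where p̄ is the mean of p1 and p2:

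power = Φ{ [ |p1 − p2|√n − 1.96√(2p̄(1 − p̄)) ] / √(p1(1 − p1) + p2(1 − p2)) }

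Example, 50% to 25%, n = 58: (0.25 × 7.616 − 1.96 × 0.6847)/0.6614 = 0.85, so power is 80%.

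| Control rate | Treated rate needed for 80% power | Absolute reduction (points) |
|---|---|---|
| 10% | none (zero treated events gives about 70%) | – |
| 20% | 3.4% | 16.6 |
| 30% | 9.5% | 20.6 |
| 40% | 16.8% | 23.3 |
| 50% | 25.0% | 25.0 |
| 60% | 34.3% | 25.8 |
| 80% | 56.0% | 24.1 |

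Power under assumed relative reductions:

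| Control rate | Risk halved | Risk cut by one third |
|---|---|---|
| 20% | 32% | 16% |
| 30% | 49% | 24% |
| 40% | 65% | 33% |
| 50% | 80% | 44% |
| 60% | 91% | 58% |
| 80% | 99.6% | 87% |

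Fisher's exact test is less favourable: 74% rather than 80% for 50% to 25%.

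**4. Mortality.** The article gives no 48-month mortality. Assumption: 20% to 40% of all 116 patients die, so D = 23.2 to 46.4 deaths. By Schoenfeld's formula, the detectable HR is exp(−2 × 2.8016/√D).

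- D = 23.2: exp(−5.603/4.817) = 0.31.
- D = 46.4: exp(−5.603/6.812) = 0.44.
- Power for HR 0.7 is Φ(0.3567√D/2 − 1.96). This is Φ(−1.10) = 14% at 23.2 deaths and Φ(−0.75) = 23% at 46.4.
- Deaths needed: HR 0.5 needs 4 × 2.8016²/(ln 0.5)², or 66 deaths, which is 57% of 116. HR 0.7 needs 247, more than twice the number of patients.

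These figures use all 116 patients. Losses before 48 months would lower the power for late outcomes.

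**The case against.** **The sentence is an estimate and cannot be refuted by arithmetic.** This stands in part. Without a stated effect there is no power figure to contradict, and the calculation that is shown is correct. A reader might infer that the article contains a false figure or an arithmetic error. The documents do not support that. The defect is an unsupported claim, which could be met only under effects nobody has stated.

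**PGD and CLAD are common.** This stands. Within the Introduction's 40% to 80% range, halving the risk reaches 80% power from a control rate of about 50%, and a one-third reduction from 80% has 87% power. A flat statement that the trial cannot deliver 80% power for PGD or CLAD would go too far.

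**PGD is measured on three days.** The plan analyses repeated binary outcomes with mixed models, so step 3 may understate power for PGD. A reader might dichotomise the primary assumptions at a ratio of 300 (50% versus 27.4%), obtain 71% power, and conclude that the claim fails for PGD on the plan's own inputs. That is only a proxy. It uses the highest ratio in 72 hours, ignores the infiltrate criterion and treats PGD as a single measurement. For the same rates averaged over three days, a design-effect approximation gives about 87% power at a within-patient correlation of 0.5 and about 77% at 0.8. Repeated measurement does not help mortality.

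**Early stopping.** The interim analysis comes "after at least 30 participants for each group have undergone LTx", so a reader might say the claim ignores a stop at about 30 per arm. The sentence is expressly tied to the full 116, and stopping is at the trial management team's discretion, so this does not count against it. Testing many secondary outcomes at .05 raises multiplicity, which is a separate matter from power.

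**The detail may sit in the full protocol or analysis plan.** Detectable differences may well be there, and their absence from an article is no fault. But the point concerns a sentence that the article does contain.

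**Conclusion.** The blanket claim is unsupported. The article derives its sample size for the primary endpoint alone and gives no effect for any secondary outcome.

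- **Mortality:** untenable unless the hazard is more than halved. This rests on an assumed 20% to 40% dead by 48 months, but a hazard ratio of 0.5 would fall short of 80% power at any overall mortality below about 57%.
- **PGD, CLAD and rejection:** tenable only with a high control rate and a large effect, about a halving from 50% or more, subject to any gain from repeated measurement of PGD. The rates and effects tried here are assumptions.
- **Continuous outcomes:** tenable only for standardised differences of about 0.52 or more.

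The primary sample size of 52, raised to 58 per arm, is not affected.

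**What to change.** Delete the sentence. Alternatively, replace it with the minimum detectable difference for each type of secondary outcome at the planned sample size, stating the assumed control rate or number of deaths behind each figure.

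In either case, say that the trial is powered for the primary endpoint only and that secondary outcomes are supportive estimates reported with 95% confidence intervals. Add that a non-significant mortality, CLAD, rejection or PGD result is not evidence of no effect.

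This is a change of wording. It needs no extra patients and leaves endpoints, alpha and conduct as they are. The only cost is a less favourable stated figure.

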#### Expected Dropout Rates

Based on clinical experience, perioperative and postoperative mortality within the first 72 hours after transplantation is expected to be low. The sample size estimation has been adjusted to account for possible losses due to dropouts. Long-term follow-up visits will coincide with standard visits, and thus we do not expect many dropouts during the long-term follow-up.

#### Interim Analysis

The DSMB will perform an interim analysis of the primary outcome after at least 30 participants for each group have undergone LTx and reached the intervention period and the 72-hour time point has been passed for the 30th participant in each group. The DSMB will use Pocock stopping boundaries (*P*<.03) as the statistical limit to guide its recommendations regarding early termination of the trial on the basis of rejecting the null hypothesis. If the *P* value for the primary outcome is below .03 at the interim analysis, then a decision will be taken by the trial management team to either stop the trial early or to continue recruitment. This has been accounted for in the sample size calculation above, and no additional adjustments for multiple testing are necessary.

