### Purpose of the Clinical Investigation

The purpose of this clinical trial is to demonstrate the superiority of cytokine filtration in improving LTx outcome, based on its effects on oxygenation ratio, plasma levels of inflammatory markers, PGD incidence and severity, lung function, kidney function, survival, and quality of life (QOL) compared with standard treatment with no cytokine filtration.

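### The interim rule hands the stop-or-continue choice to the trial management team only when P<.03, so being asked discloses a positive result while recruitment may go on

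*Protocol article*

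**What the plan says.** All references are to the Protocol article.

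- **Interim Analysis.** There is one look: "The DSMB will perform an interim analysis of the primary outcome after at least 30 participants for each group have undergone LTx" and the 30th in each group has passed 72 hours. The DSMB uses a Pocock limit of P<.03 "as the statistical limit to guide its recommendations regarding early termination of the trial on the basis of rejecting the null hypothesis". If P falls below .03, "then a decision will be taken by the trial management team to either stop the trial early or to continue recruitment".
- **Level of Significance and Power.** The Pocock level is carried to the end of the trial: "Therefore, the 2-sided α value in the final analysis will be" .03, with 80% power.
- **Sample Size.** The treatment-group "value will be 60 (SD 100) mm Hg higher (effect size) in the treatment group compared with the control group". This leads to 52 per group, raised to 58 for losses (116 in total).
- **Data Safety Monitoring Board.** The board is independent of the sponsor and carries out the interim analysis.
- **Blinding.** Those who deliver the treatment are unblinded. Outcome assessors are blinded only for follow-up visits after 1 month, and statisticians for the analyses after the study ends. The trial management team is not mentioned.
- **Primary Performance End Point.** The primary measure is the best PaO2/FiO2 ratio reached in the first 72 hours, so it falls wholly inside the unblinded period.

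**The concern.** An independent DSMB keeps comparative results away from those who run a trial for as long as patients are being enrolled. Here the board does the analysis, but the choice that follows a positive result belongs to the trial management team. The referral depends on the P value alone, so the request to decide carries the result with it. Continuing is written as an ordinary option, so the plan allows patients to be enrolled and measured after the team knows that the treatment arm has passed an efficacy limit.

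At stake is the conduct of the second part of the trial. Eligibility judgements, adherence to allocation, and the timing and recording of blood gases could all shift if expectations are known. The end point is a maximum over 72 hours in an unblinded unit, so it has little protection against that. If the final analysis were positive, a critic could ask whether patients after the interim look were handled differently from those before it, and the plan gives no answer.

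**Working it through.** **Inputs** (Protocol article, Sample Size, Level of Significance and Power, and Interim Analysis): difference 60 mm Hg, SD 100, so d = 0.6; two-sided .03 at both looks; 30 per group at the interim; 52 evaluable or 58 recruited per group at the end; 1:1 allocation.

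**1. Reproducing the plan's size.** Two-sample t test (noncentral t), d = 0.6, α = .03. At 51 per group power is 79.5%; at 52 it is 80.3%. The stated 52 reproduces. Then 52/0.9 = 57.8 and 52 × 1.1 = 57.2, so 58 follows by either rule.

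**2. Chance of crossing at 30 per group.**
- SE of the difference = 100 × √(2/30) = 25.8 mm Hg.
- Expected z = 60/25.8 = 2.324; critical z for two-sided .03 = 2.170.
- Normal approximation: Φ(2.324 − 2.170) = Φ(0.154) = 56.1%. Noncentral t with 58 df: 54.2%.
- If the true difference is 40: expected z = 1.549, crossing 26.7% (normal) or 25.7% (t). If it is 30: 15.2% (t).

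**3. What a disclosed crossing tells the team.** The smallest difference that crosses is 2.225 × 25.8 = 57 mm Hg, taking the SD as 100. Anyone with the protocol who learns of a crossing in favour of treatment can infer that the observed difference was about 57 mm Hg or more, nearly the full design effect, even if no number is passed on.

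**4. Overall α with .03 at both looks.** α = 1 − P(|Z1| < 2.170 and |Z2| < 2.170), with correlation √(30/N).

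| Final n per group | Information fraction | Overall α with .03/.03 | Constant level giving exactly .05 |
|---|---|---|---|
| 52 | 0.577 | .0494 | .0304 |
| 58 | 0.517 | .0507 | .0296 |
| 60 (equal looks) | 0.500 | .0510 | .0294 |

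Using .0294 instead leaves the required size at 52 (power 80.1%) and the crossing chance at 53.9% (t).

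**5. A stricter boundary, for comparison.** O'Brien-Fleming-type spending in the usual two-sided form: interim level = 4 × [1 − Φ(2.241/√t)], with the final level solved so that overall α = .05. Crossing and power use the normal approximation. Expected n per group is N − (N − 30) × P(cross), if every crossing ended recruitment.

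| | N = 52, Pocock .03 | N = 52, OBF-type | N = 58, Pocock .03 | N = 58, OBF-type |
|---|---|---|---|---|
| Interim level | .03 | .0063 | .03 | .0037 |
| Final level | .03 | .0480 | .03 | .0488 |
| Crossing chance | 56.1% | 34.2% | 56.1% | 28.0% |
| Two-look power | 83.2% | 86.2% | 87.0% | 89.7% |
| Expected n per group | 39.7 | 44.5 | 42.3 | 50.2 |

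The gain is about 3 points of power at the same maximum size; the price is about 5 to 8 more patients per group on average.

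**The case against.** **Advisory boards advise, and sponsors decide.** That is common, and the article says the limit guides the board's recommendations. It also does not say that a P value or estimate is passed on, and a DSMB charter or the full plan may regulate communication. This removes any claim that numbers are released. It does not remove the signal: as printed, the team's choice exists only when P<.03, and continuing is one of its two outcomes.

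**The team may not be the bedside staff.** A reader might infer that staff who know the arms and set FiO2 would learn the result. The documents do not support that. Membership is not given, and Database Management and Quality Control lists investigators and the trial management team separately. The point rests only on the disclosure to the team in a trial that is unblinded at the bedside.

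**54-56% is not the chance of stopping.** Correct. It is the chance of crossing a non-binding limit, and only if the assumed 60 mm Hg is true. For the disclosure problem, crossing is the relevant event.

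**The .03 level.** A reader might infer that rounding .0294 up to .03 inflates α. It does not matter here. At the planned 52 evaluable per group overall α is below .05, the excess at 58 is 0.0007, and a look later than 30 per group lowers it further.

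**Pocock is a legitimate choice.** It is prespecified, the final .03 is in the sample size, and two-look power exceeds 80%. Overestimation after early stopping belongs to group-sequential designs generally. A reader might also infer that stopping would undo the wider aims on "PGD incidence and severity, lung function, kidney function, survival, and quality of life (QOL) compared with standard treatment". Ending recruitment early would leave fewer patients for them: at 30 per group an outcome with d = 0.6 has about 63% power at α .05. But these are secondary objectives, and nothing says that follow-up of enrolled patients would be cut. The choice of boundary is a trade-off, not an error.

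**Conclusion.** The point holds as a flaw in how the interim result is communicated. The text makes a stop-or-continue decision by the trial management team conditional on P<.03, so the team learns that the boundary was crossed, and recruitment may then proceed. Under the plan's assumptions this has a 54-56% chance at 30 per group; it falls to about 26% at a true difference of 40 mm Hg. These figures assume SD 100, a look at exactly 30 per group and an unadjusted comparison. The planned covariate adjustment could raise them slightly, but no covariate correlation is given.

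The size of any resulting bias cannot be computed from the document, because the team's membership and contact with the sites are not stated. The case for change is that the exposure is likely and avoidable at almost no cost. The plan's α, its sample size and the use of a Pocock boundary stand.

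**What to change.** **Recommended.** Amend the Interim Analysis section in three respects:
- The independent DSMB applies the boundary, and any discretion to go on after a crossing is exercised within the board.
- The board sends the trial management team only 'stop' or 'continue'.
- No P value, estimate or boundary status is released to the team unless the trial stops.

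It would help to state in the same place who sits on the team and whether its members are blinded to comparative data. The cost is a short amendment with matching text in the analysis plan and any DSMB charter, and no added patients. The trial management team gives up its own discretion after a crossing.

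**Optional.** Replace the Pocock limit with an O'Brien-Fleming-type spending boundary computed from the actual information fraction: interim about .004-.006, final about .048-.049. The chance of crossing would fall to about 28-34% and two-look power would rise by about 3 points at the same maximum size. The cost is a larger expected sample and a lower chance of an early answer, so this is for the sponsor to weigh.

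No change to .03 is needed on α grounds if Pocock is kept.

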#### Randomization

An allocation sequence will be created in advance by an independent statistician and linked to a digital randomization module in the eCRF. As each patient is included by the investigator, the next number in the sequence will be revealed and the patient will be assigned to the intervention indicated therein. Randomization is performed using a web-based system (REDCap; Research Electronic Data Capture; Vanderbilt University) and patients are randomized in a 1:1 ratio to 1 of the 2 groups. Randomization will be done using random permuted blocks of varying size, stratified by site, gender, and age.

